We intend to carry out a prospective, randomized controlled trial (RCT) to examine the effects and mechanisms of three months of Baduanjin training on the risk of falls in elderly individuals with MCI. The main goal of this trial is to verify the intervention effect of Baduanjin training on the risk of falls in elderly people with MCI and to explore the mechanism of Baduanjin in reducing the risk of falls in elderly individuals with MCI from the perspective of functional connectivity of the vestibular neural network.

We hypothesize that Baduanjin training could reduce the risk of falls in older adults with MCI compared with brisk walking and no specific exercise intervention. With neuroimaging, we hypothesize that differential functional connection changes will be observed between the Baduanjin training and the brisk walking group and the health education group.

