### Sample size

The results of a previous systematic review showed that the standardized mean difference of the fall risk of the elderly with Baduanjin exercise intervention was − 0.59 [-0.83, -0.35] [36], which was used as a reference to calculate the sample size of the effect size of this study. The significance level will be set at α = 0.05, and the power will be 0.80. Using Gpower 3.9 software, we calculated that a sample size of at least 20 patients per group is needed, and considering a 20% drop-out rate, which means 24 patients per group, the total sample size required for this study is 72 cases.

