### Statistical analysis

The data of this study will be statistically analysed using SPSS 26.0 software. All statistical tests will be performed using a two-sided test with an α value of 0.05, and we will consider the test results statistically significant when the resulting p value is ≤ 0.05.Count data will be described using frequencies, percentages, or composition ratios. The continuous data will be described by mean ± standard deviation or median. This study will include multiple imputation for missing data and an intention-to-treat analysis. One-way ANOVA will be used for data satisfying a normal distribution, teh rank sum test will be used for those not satisfying a normal distribution, and the chi-square test will be used for count data.

Primary outcomes will be further analysed with the mixed-effect linear model with restricted maximum likelihood to determine the interaction effect between group and time. In this model, the independent variables are group (Baduanjin group, brisk walking group, and health education group), time (different measurement time points), sex, age, education level and other confounding factors, all of which will be analysed as covariates.

Preprocessing of the fMRI data was performed using the Functional Connectivity Toolbox (CONN) pipeline version 21a (www.nitrc.org/projects/conn, accessed on 5 September 2022). The preprocessing included slice-timing correction, segmentation, normalization, smoothing (Gaussian kernel = 8 mm), and bandpass filtering (0.008 to 0.08 Hz) [37]. We will implement a functional connectivity analysis of the corticocortical vestibular network based on the region of interest (ROI). The selection and specific analysis method of the corticocortical vestibular network ROI is similar to that of a previous study which was conducted in 2022 [38].

Adverse effects (AEs) will be analysed using the χ^2^ test or Fisher’s exact test. If formal statistical analyses between groups cannot be performed due to the lack of power, AEs will be tabulated and summarized using descriptive statistics.

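### Twenty patients per group does not follow from the stated inputs: at SMD 0.59, two-sided α 0.05 and 80% power, an unadjusted two-arm comparison at one visit needs 47 per group

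*Protocol article*

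**What the plan says.** All of this is in the protocol article.

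- **Effect size (Sample size).** The "standardized mean difference of the fall risk of the elderly with Baduanjin exercise intervention" is given as −0.59 with interval −0.83 to −0.35, and serves as the reference for the calculation.
- **Error rates (Sample size).** "The significance level will be set at α = 0.05, and the power will be 0.80".
- **Result (Sample size).** From G*Power, "we calculated that a sample size of at least 20 patients per group is needed". Then, "considering a 20% drop-out rate, which means 24 patients per group, the total sample size required for this study is 72 cases".
- **Sidedness (Statistical analysis).** "All statistical tests will be performed using a two-sided test with an α value of 0.05".
- **Hypothesis (end of Background).** Baduanjin is expected to lower fall risk "compared with brisk walking and no specific exercise intervention", so the question lies between groups and has two comparators.
- **Analysis (Statistical analysis).** One-way ANOVA or a rank sum test, then for the primary outcome a mixed linear model with a group-by-time interaction. Study design gives four visits, three of them after baseline.

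The Sample size section names no test, comparison, number of visits or within-person correlation.

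**The concern.** The article prints both its inputs and its result, so a reader can put one into the other. For a two-sided between-group comparison at an SMD of 0.59, 20 per group is less than half of what the standard calculation returns. This is a mismatch between printed figures, not a missing detail.

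The calculation is the only justification given for the trial's size. If the 80% is taken at face value, a non-significant result would be read as fairly strong evidence against a difference of 0.59. If the real power is nearer one half, that reading is wrong.

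**Working it through.** **Inputs.** From Sample size: d = 0.59 (interval 0.35 to 0.83), α = 0.05, power 0.80, n = 20 evaluable and 24 enrolled per group. From Statistical analysis: two-sided tests. Correlations below are assumptions; the article gives none.

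**1. Attempt to reproduce 20: two arms, one visit, unadjusted.**

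Normal approximation: n = 2(z₀.₉₇₅ + z₀.₈₀)² / d² = 2(1.960 + 0.842)² / 0.59² = 45.1, so 46 per group.

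Exact noncentral t, with 2n − 2 degrees of freedom and noncentrality d√(n/2): power is 79.9% at n = 46 and 80.8% at n = 47. **The requirement is 47 per group** (37 if one-sided). The figure of 20 is not reproduced.

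**2. Power of the same two-sided test at the stated sizes.**

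| n per group | d | Noncentrality | Power |
|---|---|---|---|
| 20 | 0.59 | 0.59 × √10 = 1.866 | 44.4% |
| 24 | 0.59 | 0.59 × √12 = 2.044 | 51.6% |
| 20 | 0.35 | 0.35 × √10 = 1.107 | 19.0% |
| 20 | 0.83 | 0.83 × √10 = 2.625 | 72.5% |

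Solving for d at 80% power gives 0.91 with 20 per group and 0.83 with 24. The second equals the upper limit of the cited interval.

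**3. Three-group one-way ANOVA**, noncentrality 3n·f²:

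| Conversion of 0.59 to f | f | n per group | Power at 20 |
|---|---|---|---|
| d/2 (the two-group conversion) | 0.295 | 38 | 50% |
| One arm differs: d√2/3 | 0.278 | 43 | 45% |
| Evenly spaced means: d/√6 | 0.241 | 57 | 35% |

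None gives 20.

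**4. What has to be added to reach 80% with 20 per group.** Let ρ be the correlation between visits. Replace d by d divided by the residual SD.

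- *Baseline-adjusted, one follow-up:* d/√(1 − ρ²). At ρ = 0.5, 0.59/√0.75 = 0.681 and power is 56%. At ρ = 0.7 it is 72%. Reaching 80% needs ρ of about 0.76.
- *Change from baseline, one follow-up:* d/√(2(1 − ρ)). At ρ = 0.5 the divisor is 1, so 47 per group are still needed. At ρ = 0.8, 0.59/√0.4 = 0.933 and 20 per group suffice.
- *Baseline-adjusted mean of three follow-ups, equal correlations, constant effect:* variance (1 + 2ρ)/3 − ρ². At ρ = 0.5 this is 0.667 − 0.25 = 0.417, so d becomes 0.59/√0.417 = 0.914 and power is 80%. At ρ = 0.3 power is 78%; at 0.7 it is 90%.
- *Omnibus 3-group by 4-visit interaction* (6 degrees of freedom, equal correlations), with Baduanjin 0.59 better than both other arms at all three follow-ups and no difference at baseline: power at 20 per group is 32%, 45% and 70% for ρ = 0.3, 0.5 and 0.7. With evenly spaced arms it is 24%, 34% and 55%.
- *G*Power-type repeated-measures interaction with f = 0.295 entered directly:* 5 to 20 per group for 2 to 4 visits and ρ from 0 to 0.7. Here f describes the interaction itself and is not the SMD of 0.59 carried through the trial's visit pattern.

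**The case against.** The best reply is that 44% belongs to a test that is not the planned primary model. The trial measures the primary outcome at baseline and three later visits and plans a mixed model, which uses more information than one unadjusted visit. Under a constant effect and a correlation of 0.5, the baseline-adjusted mean of the three follow-ups has 80% power with exactly 20 per group. This stands. A reader might infer that the design cannot have 80% power at SMD 0.59; the article does not support that, because it gives neither the correlation nor the contrast. The same reply does not rescue the printed statement: no repeated-measures basis is stated there, and the omnibus interaction that Statistical analysis does describe stays below 80% in the cases above with ρ up to 0.7.

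It can also be said that a condensed article may leave the test family and correlation to a full protocol. That would excuse silence. It does not excuse printing inputs and a result that do not agree.

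Three other inferences are tempting and go too far.

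- *A one-sided paired t test was used.* It returns exactly 20 at d = 0.59 (25 if two-sided), but nothing in the article says it was the method. A match found by search is not evidence.
- *A null result is more likely than not even if the effect is real.* This holds for the unadjusted test with 20 per group (44%). It does not hold with 24 (52%) or, at 20 per group, with baseline adjustment (56% at ρ = 0.5, 72% at ρ = 0.7).
- *The effect against brisk walking will be smaller.* The article gives no figure for it and hypothesises superiority over both comparators without ranking them.

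**Conclusion.** The point holds in this form: 20 per group is not what the printed inputs give under two-sided testing. The shortfall for a single-visit analysis is large: 47 needed for an unadjusted two-arm comparison, and 38 to 57 for a three-group ANOVA depending on how 0.59 is spread over the arms. The 44% (20 per group) and 52% (24 per group) are conditional on the unadjusted two-arm, single-visit test at a true SMD of 0.59. They make no allowance for testing two comparators.

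Whether the planned mixed model reaches 80% is open. It depends on the correlation, the contrast tested and whether the effect is constant over follow-up, none of which the Sample size section states. The claim of 80% power is therefore unsupported as written, rather than shown to be false for every analysis the trial might run. It needs correcting because it is the only stated basis for the trial's size.

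**What to change.** Keep N = 72 and correct the Sample size section. Name the test and the comparison to which the calculation refers. Then do one of the following.

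- **(a)** State the repeated-measures basis, with the number of visits and the assumed correlation, and show that it gives 80% power for the planned model.
- **(b)** Withdraw the claim of 80% power at SMD 0.59. State the power available with 20 evaluable per group: about 44% unadjusted at one visit, or about 56% with baseline adjustment if the correlation is 0.5. Give the SMD detectable with 80% power in the unadjusted test, 0.91.

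The choice of powered comparison is the sponsor's. In either case, report each Baduanjin comparison with a confidence interval, so that a non-significant result is not taken as evidence of no effect.

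The cost is a rewritten paragraph and, under (b), a less favourable stated power. No extra patients are needed.

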## Methods

### Study design

The design of this study is a three-arm RCT in a 1:1:1 allocation ratio with allocation concealment and assessor blinding. A total of 72 eligible participants will be randomly assigned to the 12-week Baduanjin exercise intervention (60 min per session, three sessions per week), the 12-week brisk walking group(60 min per session, three sessions per week) or the 12-week health education group. In addition to the MRI scans, which will be measured before and after the intervention,other primary and secondary outcomes will be assessed at baseline, 6 weeks, and 12 weeks (at the end of the intervention) and after an additional 12-week follow-up period. The study procedure and outcome assessment schedule for this trial are presented in Figs. 1 and 2.

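### The drop-out allowance multiplies 20 by 1.2 instead of dividing by 0.8, so 24 per group falls short of the plan's own minimum of 20 at 20% loss

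*Protocol article*

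**What the plan says.** The Sample size section of the protocol article gives three linked figures. It sets the base: "we calculated that a sample size of at least 20 patients per group is needed". It then allows for loss: "considering a 20% drop-out rate, which means 24 patients per group". It closes with the total: "the total sample size required for this study is 72 cases". The total agrees with the design, described under Study design as a "three-arm RCT in a 1:1:1 allocation ratio", since 3 × 24 = 72.

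No inflation formula is given. Nowhere else does the article state a different drop-out rate or another route to 24.

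**The concern.** The text presents 24 as what a 20% drop-out rate implies for a minimum of 20. A drop-out rate applies to the participants enrolled, so the enrolled number must still be at least 20 after a fifth of it is removed. Twenty-four is not. It is what results from adding 20% of the target to the target, which is a different operation.

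This sentence is the article's justification for enrolling 72. As written, it tells the reader that the minimum is protected at the assumed loss, and it is not. The same formula would also under-inflate any revised base, so correcting the base figure alone would leave this error in place.

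**Working it through.** **Inputs (protocol article)**
- Minimum per group before loss: 20 (Sample size).
- Drop-out rate: 20% (Sample size).
- Enrolled: 24 per group, 72 in total (Sample size).
- Three equal arms (Study design).
- Standardised mean difference −0.59, interval −0.83 to −0.35; α = 0.05; power 0.80 (Sample size).
- Two-sided tests (Statistical analysis).

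**Reproducing the stated figure**
- n × (1 + d) = 20 × 1.20 = 24 per group; 3 × 24 = 72. This matches exactly.

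**What 24 delivers at the assumed loss**
- 24 × (1 − 0.20) = 19.2 per group.
- 72 × 0.80 = 57.6 overall, against 3 × 20 = 60.

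**The inflation that meets the stated minimum**
- n / (1 − d) = 20 / 0.80 = 25 per group; 3 × 25 = 75.
- Check: 25 × 0.80 = 20.0.
- Shortfall: 1 per group and 3 in total; 3 / 72 = 4.2% of the planned total.

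**The loss that 24 can absorb**
- 1 − 20/24 = 0.167, that is 16.7%.

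**Effect on power** (two-sample t-test, two-sided, α = 0.05)

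| Per group with outcomes | Power at SMD 0.59 | SMD detectable at 80% power |
|---|---|---|
| 19 | 42.5% | 0.934 |
| 19.2 | 42.9% | 0.929 |
| 20 | 44.4% | 0.909 |

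Only the differences between rows belong to this point: about 2 percentage points of power, and 0.025 in the detectable difference between 20 and 19. The level of the whole table reflects the base of 20. On this test an SMD of 0.59 needs 46 to 47 per group for 80% power.

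**The same comparison on the plan's own premise.** Suppose that 20 per group does give 80% power, which on this test means a true SMD of 0.909. Power is then 78.3% at 19.2 and 77.8% at 19, again a loss of about 2 points.

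**Chance that one arm keeps at least 20.** If participants drop out independently with probability 0.20 (an assumption made here for illustration), the binomial probability is 46% with 24 enrolled and 62% with 25.

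**Carry-over to a corrected base.** With a base of 47, multiplying gives 47 × 1.2 = 56.4, rounded up to 57; dividing gives 47 / 0.8 = 58.75, rounded up to 59.

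**The case against.** The strongest reply is that the gap makes no practical difference. It is one participant per group and about two points of power, which is small beside the uncertainty in the 20% guess and in an effect size whose interval runs from 0.35 to 0.83 in absolute value. This stands as a statement of size. It does not make the stated figure right.

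A second reply concerns who is analysed. The Statistical analysis section says: "This study will include multiple imputation for missing data and an intention-to-treat analysis". It also plans a mixed model for the primary outcome, which is measured at four time points. A participant lost after week 6 still contributes earlier data, and all 24 per group may enter the analysis. This stands as a point of wording: 19 is the expected number with observed final outcomes, not the number analysed. It does not rescue the arithmetic. Imputation does not restore the information lost with missing outcomes, and by inflating for drop-out the plan itself treats observed outcomes as what must reach 20.

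A third reply is that the poor power figures arise from the base of 20, and that recalculating the base would make the choice between 24 and 25 moot. The first part is correct, and the figures are attributed that way here. The second part is not a defence, because the formula would under-inflate the new base too.

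**Conclusion.** The stated drop-out allowance is wrong as written. At the plan's own 20% rate, 24 per group is expected to leave 19.2 with outcomes, not the required 20. The enrolment that matches the text is 25 per group, 75 in total.

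The inflation result rests only on the three figures printed in the Sample size section. The power figures additionally assume a two-sided two-sample t-test between two arms, with no credit for repeated measures or covariates. The consequence is small and does not by itself undermine the trial. Correcting it does not secure 80% power either: even with 25 observed per group, power at an SMD of 0.59 is about 53% on the same test. It should still be corrected, because the sentence claims a protection that the numbers do not give.

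**What to change.** Keep 72 and rewrite the sentence, for example: *Enrolling 24 per group allows for up to 16.7% drop-out if 20 per group are to have observed outcomes; at 20% drop-out about 19 per group are expected.* Follow it with power and the detectable difference at 19 per group: SMD 0.93 at 80% power, and 42% power at SMD 0.59, for a two-sided two-sample t-test at α = 0.05. If the base figure is recalculated, inflate it by dividing by 1 − 0.20.

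The cost is one or two sentences and slightly less favourable stated figures. No extra recruitment or design change follows. The alternative of enrolling 75 would make the present wording true at the cost of three more participants, but it would gain little while the base of 20 is unresolved.

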### Statistical analysis

The data of this study will be statistically analysed using SPSS 26.0 software. All statistical tests will be performed using a two-sided test with an α value of 0.05, and we will consider the test results statistically significant when the resulting p value is ≤ 0.05.Count data will be described using frequencies, percentages, or composition ratios. The continuous data will be described by mean ± standard deviation or median. This study will include multiple imputation for missing data and an intention-to-treat analysis. One-way ANOVA will be used for data satisfying a normal distribution, teh rank sum test will be used for those not satisfying a normal distribution, and the chi-square test will be used for count data.

Primary outcomes will be further analysed with the mixed-effect linear model with restricted maximum likelihood to determine the interaction effect between group and time. In this model, the independent variables are group (Baduanjin group, brisk walking group, and health education group), time (different measurement time points), sex, age, education level and other confounding factors, all of which will be analysed as covariates.

Preprocessing of the fMRI data was performed using the Functional Connectivity Toolbox (CONN) pipeline version 21a (www.nitrc.org/projects/conn, accessed on 5 September 2022). The preprocessing included slice-timing correction, segmentation, normalization, smoothing (Gaussian kernel = 8 mm), and bandpass filtering (0.008 to 0.08 Hz) [37]. We will implement a functional connectivity analysis of the corticocortical vestibular network based on the region of interest (ROI). The selection and specific analysis method of the corticocortical vestibular network ROI is similar to that of a previous study which was conducted in 2022 [38].

Adverse effects (AEs) will be analysed using the χ^2^ test or Fisher’s exact test. If formal statistical analyses between groups cannot be performed due to the lack of power, AEs will be tabulated and summarized using descriptive statistics.

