**Methods:**

In this prospective study, outcome assessor-blind, three-arm randomized controlled trial, a total of 72 eligible participants will be randomly allocated (1:1:1) into the 12-week Baduanjin exercise intervention (60 min per session, three sessions per week), the 12-week brisk walking group(60 min per session, three sessions per week) or the 12-week health education group. Primary outcome is the Fall-Risk Self-Assessment Questionnaire(FRQ), and secondary outcomes are fall efficacy index, gait assessment, balance function, lower limb muscle strength, cognitive function, activities of daily living(ADL) and MRI scans. In addition to the MRI scans, which will be measured before and after the intervention,other primary and secondary outcomes will be assessed at baseline, 6 weeks, and 12 weeks (at the end of the intervention) and after an additional 12-week follow-up period. The mixed linear model will be conducted to observe the intervention effects.

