### Outcome assessment

The variables in this trial will consist of basic information, primary outcomes, and secondary outcomes. The basic characteristics will be measured at baseline (1–2 weeks before randomized allocation). In addition to the MRI scans, which will be measured before and after the intervention,other primary and secondary outcomes will be measured at baseline, in the middle of the intervention period (6 weeks after randomization), at the end of the intervention period (12 weeks after randomization) and after an additional 12-week follow-up period. All primary and secondary outcomes will be assessed by the experienced staff at the People’s Hospital Baoan Shenzhen, who will be blinded to the allocation results of participants. A summary of all planned measurements for this trial is shown in Fig. 2.

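### The mixed model is named for the primary outcome only, and no stated analysis adjusts for the participant's own baseline value, which costs precision

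*Protocol article*

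**What the plan says.** The Statistical analysis section of the protocol article first gives a general rule: "One-way ANOVA will be used for data satisfying a normal distribution", a rank sum test where normality fails, and a chi-square test for counts. It does not say which outcomes, visits or values (raw or change) this rule covers.

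It then adds the model: "Primary outcomes will be further analysed with the mixed-effect linear model with restricted maximum likelihood to determine the interaction effect between group and time". The named terms are group, "time (different measurement time points), sex, age, education level and other confounding factors, all of which will be analysed as covariates". Baseline FRQ is not named among them.

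The Outcome assessment section sets the visits: "other primary and secondary outcomes will be measured at baseline, in the middle of the intervention period (6 weeks after randomization"), then at 12 weeks and after a further 12 weeks of follow-up. MRI is the exception, taken before and after the intervention, and it has its own region-of-interest connectivity analysis.

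The Methods part of the abstract lists primary and secondary outcomes together and closes with "The mixed linear model will be conducted to observe the intervention effects", with no restriction to the primary outcome.

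**The concern.** Fall efficacy, gait, balance, sit-to-stand, MoCA and Barthel scores are each collected four times. The wording "Primary outcomes will be further analysed with the mixed-effect linear model" adds the mixed model to the general rule for the primary outcome alone. ANOVA or rank sum is then the only between-group method stated for these secondary outcomes. A one-way ANOVA has group as its single factor. Even if run on change scores, it handles one visit at a time and does not adjust for baseline. The abstract points the other way, so a reader cannot tell which analysis the trial has committed to.

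For the FRQ the issue is narrower. Baseline is one of the measurement times in a group-by-time model, so the treatment contrast at week 12 is a difference in change from baseline. A contrast adjusted for the participant's own baseline estimates the same effect with a smaller variance. In a trial planned on 20 evaluable participants per arm, that difference matters.

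**Working it through.** **Inputs from the Sample size and Statistical analysis sections.** Standardised mean difference 0.59 in absolute value; two-sided α = 0.05; target power 0.80; 20 evaluable per arm.

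**Assumed input.** The documents give no correlation ρ between baseline and week-12 scores. I take 0.3, 0.5 and 0.7, with equal variances at the two visits.

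**The plan's own figure.** For two arms compared on follow-up values, the normal approximation gives n = 2(1.960 + 0.842)² / 0.59² = 45.1, so 46 per arm (47 with the t distribution). The stated 20 per arm is not reproduced. At 20 per arm this comparison has 44% power (noncentral t, 38 degrees of freedom). How 20 was reached is a separate matter. Here 20 serves only as the planned evaluable number.

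**Variance of the week-12 contrast, relative to follow-up values alone.**
- Follow-up values only: 1
- Change from baseline (group-by-time with baseline as a response): 2(1 − ρ)
- Adjusted for own baseline: 1 − ρ²
- Ratio of change to adjusted: 2(1 − ρ)/(1 − ρ²) = 2/(1 + ρ)

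| ρ (assumed) | Follow-up only | Change | Adjusted | Change ÷ adjusted |
|---|---|---|---|---|
| 0.3 | 1.00 | 1.40 | 0.91 | 1.54 |
| 0.5 | 1.00 | 1.00 | 0.75 | 1.33 |
| 0.7 | 1.00 | 0.60 | 0.51 | 1.18 |

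**Power at 20 per arm.** The effective effect size is 0.59/√(variance factor). At ρ = 0.5, for example, the adjusted value is 0.59/√0.75 = 0.681. Noncentral t, 38 degrees of freedom:

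| ρ (assumed) | Follow-up only | Change | Adjusted |
|---|---|---|---|
| 0.3 | 44% | 34% | 48% |
| 0.5 | 44% | 44% | 56% |
| 0.7 | 44% | 65% | 72% |

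The ratio 2/(1 + ρ) exceeds 1 for every ρ below 1, so adjustment always beats change. The factor 1 − ρ² is below 1 for any non-zero ρ, so adjustment also beats follow-up values alone.

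**Correlation needed for 80% power by adjustment alone.** The normal approximation requires 1 − ρ² = 20/45.1 = 0.443, so ρ = 0.75. With noncentral t, power is 78% at ρ = 0.75 and 80% at ρ = 0.76.

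**Reach of these figures.** The effect of 0.59 is for fall risk. The documents give no expected effect for the secondary outcomes, so only the variance factors carry over to them.

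**The case against.** The strongest reply is that the FRQ model already uses baseline. This stands. A reader might infer that the primary analysis ignores baseline, or that chance baseline differences pass straight into the week-12 FRQ comparison. The documents do not support that: with baseline as a measurement time, the interaction subtracts it. The open-ended reference to other confounders also means a baseline covariate is not expressly excluded. What remains is the efficiency gap between change and adjustment.

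A reader might also infer that every secondary outcome gets a purely cross-sectional test. The text does not say which values enter the ANOVA, so this is an inference, and it is wrong for MRI, which has its own analysis. Nor is any bias shown: under randomisation, chance imbalance is already reflected in the standard error.

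It can be said that such detail belongs in a separate analysis plan, and that a one-line abstract need not match the methods in full. This stands only in part. The Statistical analysis section does not merely stay silent: it names the method, the outcome class that gets the model, and most of its covariates.

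Finally, a rank test is defensible for scores near a ceiling. Normal daily living is a diagnostic criterion here, so Barthel scores are likely to cluster near 100. Whether to keep a rank test for such scores is a matter of preference, and I do not count its use as an error.

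**Conclusion.** The point holds as one of precision and clarity. As written, the continuous secondary outcomes other than MRI have no stated analysis with a baseline covariate or repeated visits, and the abstract and the Statistical analysis section differ on how far the mixed model reaches. For the FRQ, the apparent change-from-baseline contrast is valid but has 1.18 to 1.54 times the variance of the adjusted one over correlations of 0.7 down to 0.3. That is 7 to 14 percentage points of power at 20 per arm.

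These sizes rest on assumed correlations, equal variances, complete data at 20 per arm, and baseline entering the FRQ model as a response with time as categories. Adjustment would not by itself deliver the stated 80% power unless the correlation is about 0.75 or higher, so it does not settle the sample-size question. The change is worth making because it is cheap. The planned tests are not invalid.

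**What to change.** In the Statistical analysis section, specify one REML mixed model for the FRQ and for each continuous secondary outcome other than MRI:

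- Response: the post-baseline visits (week 6, week 12, and the follow-up 12 weeks later).
- Terms: group, visit as a category, group-by-visit, and the participant's own baseline value as covariate, alongside the covariates already named. A model with a common baseline mean across arms is an equivalent choice.
- Report: adjusted between-group differences at week 12 with 95% confidence intervals.
- Sensitivity: keep a rank-based or bootstrap analysis for skewed or ceiling-bound scores such as the Barthel Index.

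State what the one-way ANOVA and rank sum tests are still for, and make the abstract and the Statistical analysis section name the same model for the same outcomes.

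The cost is wording only: the visits are already scheduled and a mixed model is already planned. There is a small downside. A linear model may fit ceiling-bound scores poorly, and the gain is small where the baseline correlation is low: at 0.3 the variance falls only 9% against follow-up values alone.
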